The second diagnostic challenge is the high prevalence of asymptomatic bacteriuria (ASB) in older people. Approximately 20%–50% of older women have ASB,^13^ of which 90% have concomitant pyuria.^14 15^ This phenomenon limits the diagnostic utility of the second key component of UTI diagnosis, pyuria and bacteriuria-based urinalysis, in this patient population. Previous research in older women showed that the current pyuria cut-off level of 10 cells per µL has a specificity of only 36%.^16^ The diagnostic challenge is even greater in primary care and long-term care facilities which often have only a limited diagnostic array, such as dipsticks available. This is problematic considering that the majority of UTIs are treated in these healthcare facilities. The current inaccuracy in diagnostic UTI workup can result in both over- and underdiagnosis of UTIs. Overdiagnosis drives inappropriate antibiotic use and the development of antimicrobial resistance, while underdiagnosis can result in delayed treatment, increased morbidity and mortality, and longer hospital stays.^17^

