### Statistical analysis

#### Sample size

Power analyses are based on the results from the pilot study.^22^ For the biomarker panel, specificity was 91% at a sensitivity of 88%; however, power analysis was based on individual biomarkers to have an adequate sample size for assessment of both the individual markers and the panel. For individual biomarkers, sensitivity ranged from 76% to 87%, and specificity ranged from 72% to 95%. Lower bounds were used for the calculations, to ensure an adequate sample size. To assess specificity, with an α of 0.05, with (1 − α) % confidence level and a maximum marginal error of estimate of 0.10 (δ) for constructing CI of true value of specificity, assuming a value of 72% and using the normal approximation, and a disease prevalence of 30%, the total N needs to be 110. For sensitivity, using an assumption of sensitivity 76%, N would be 234.^27^ With an estimated drop-out of 5%, 246 patients need to be included.

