#### Analysis of outcome measures

All statistical analyses will be performed using IBM SPSS V.29. Baseline characteristics will be summarised by standard descriptive statistics.

Areas under the receiver operating characteristics (ROC) curves for identifying UTI will be calculated to assess the diagnostic power of the individual biomarkers. For each biomarker, the optimal cut-off will be determined based on the ROC curves, and the associated sensitivity and specificity, positive and negative predictive values, and positive and negative likelihood ratios will be reported. An additional logistic regression analysis will be performed to assess the value of combination(s) of biomarkers, aiming at a minimal sensitivity and specificity of 80%. For urine leukocytes, the above-mentioned parameters will be reported for a cut-off of 200 leukocytes/µL.

Subgroup analyses will be performed to assess the performance of biomarkers in males and females, different settings (hospital, primary care setting and long-term care) and different clinical presentations (systemic symptoms vs localised symptoms). Categorical values will be compared using the Fisher exact test or Pearson χ2 test.

Additional comparative analyses will be performed to compare biomarker levels in UTI with and without systemic symptoms. To assess the correlation between biomarker levels and time to resolution of symptoms and length of hospital stay, Pearson’s correlation coefficient will be used. For the calculation of the association between biomarker levels and complications of UTI and recurrence of UTI, logistic regression will be used.

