### Future implications

Currently, there is no reliable diagnostic tool to diagnose UTI in older adults. To address this unmet need, a point-of-care (POC) test would be ideal, one that can be easily deployed across different healthcare settings, particularly outside the hospital. The UTI-GOLD study aims to identify the most appropriate biomarker(s) signature for a POC test. Once a POC test is developed, the test must be implemented in a study to evaluate its impact on patient outcomes in daily clinical practice.

With validated and reliable diagnostic markers for UTIs in older adults, timely and appropriate treatment can be improved, reducing the negative consequences of over- and underdiagnosis. The development of a POC test based on these markers could significantly contribute to antimicrobial stewardship. Consequently, such a test has the potential to positively impact patient outcomes, lower healthcare costs and revolutionise the care for patients with UTIs globally.

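### The planned analysis does not compare pyuria at 200/µL with 10/µL, or the biomarkers with the leucocyte count, within patients, although the study's rationale is improvement on current testing

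*Protocol article*

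**What the plan says.** The Protocol article (Analysis of outcome measures) gives each biomarker an AUC, a cut-off chosen from the ROC curve and the accuracy measures at that cut-off. Combinations go into a logistic regression, with sensitivity and specificity of at least 80% as the goal. For pyuria: "For urine leukocytes, the above-mentioned parameters will be reported for a cut-off of 200" leucocytes/µL. Outcome measures lists the same index tests as primary outcomes.

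The comparisons that are named are between subgroups (sex, setting, presentation) and between UTI with and without systemic symptoms. None is between two index tests, or two cut-offs, in the same patients.

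The rationale is comparative. The Introduction states: "Previous research in older women showed that the current pyuria cut-off level of 10 cells per" µL has a specificity of only 36%, and it argues that a higher, age-specific cut-off could make existing tests perform better. Under Future implications: "The UTI-GOLD study aims to identify the most appropriate biomarker(s) signature for a POC test".

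The sample size targets the precision of single accuracy figures: "power analysis was based on individual biomarkers to have an adequate sample size for assessment of both the individual markers and the panel".

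**The concern.** Current pyuria testing is described as too unspecific, and the new cut-off and biomarkers are put forward as the remedy. As written, the results would give accuracy for pyuria at 200/µL and for each biomarker or panel, with nothing at 10/µL and no estimated difference.

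Two facts in the article make this matter.

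- The 36% specificity at 10/µL comes from older women. UTI-GOLD enrols men and women in hospitals, general practices and long-term care facilities. Without a 10/µL result in this cohort, the gain from 200/µL could be judged only against a figure from a different population.
- In the pilot, pyuria at 200/µL had 89% sensitivity and 86% specificity, and the panel 88% and 91%. Pyuria alone passed the 80%/80% mark set for combinations. A panel that reaches that mark has not been shown to add to a routine count, yet it needs mass spectrometry and ELISA.

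**Working it through.** **Reproducing the plan's sample size.** Inputs (Sample size): "with an α of 0.05", "a maximum marginal error of estimate of 0.10", specificity 72%, sensitivity 76%, prevalence 30%, drop-out 5%. Formula: n = 1.96² × p(1 − p) / 0.10², divided by the share of patients without or with UTI.

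- Specificity: 1.96² × 0.72 × 0.28 / 0.01 = 77.4; 77.4 / 0.70 = 110.6 (stated 110).
- Sensitivity: 1.96² × 0.76 × 0.24 / 0.01 = 70.07; 70.07 / 0.30 = 233.6 (stated 234).
- Drop-out: 234 × 1.05 = 245.7 (stated 246).

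The figures reproduce to within rounding. They concern one proportion at a time and include no comparison.

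**Numbers available.** 234 evaluable patients at 30% prevalence give about 70 with UTI and 164 without.

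**Half-width of a paired difference.** 1.96 × √[(disc − d²) / n], where d is the difference and disc the share of patients in whom the two results disagree.

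*200 v 10/µL, specificity.* 86% v 36%, so d = 0.50. The cut-offs are nested: a count above 200 is also above 10. All disagreement therefore runs one way and disc = 0.50. Half-width = 1.96 × √[(0.50 − 0.25) / 164] = 0.077. The difference is 50 ±7.7 points.

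*200 v 10/µL, sensitivity.* The value at 10/µL is not given. Assuming 93% to 100% against 89%, the loss is 4 to 11 points:

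- 4 points: 1.96 × √[(0.04 − 0.0016) / 70] = 0.046
- 11 points: 1.96 × √[(0.11 − 0.0121) / 70] = 0.073

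*Panel v pyuria at 200/µL, specificity.* 91% v 86%, so d = 0.05. Discordance is not given. Its minimum is 5%. If the two tests are independent among patients without UTI, it is 0.91 × 0.14 + 0.86 × 0.09 = 0.205.

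- disc 0.05: 1.96 × √[(0.05 − 0.0025) / 164] = 0.033
- disc 0.205: 1.96 × √[(0.205 − 0.0025) / 164] = 0.069

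Over the same range, the power of a McNemar test at this size runs from 82% down to 29%. Between 155 and 641 patients without UTI would be needed for 80% power.

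*Panel v pyuria at 200/µL, sensitivity.* 88% v 89%, so d = 0.01, n = 70. Discordance runs from 0.01 to 0.88 × 0.11 + 0.89 × 0.12 = 0.204, and the half-width from 2.3 to 10.6 points.

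**The case against.** The strongest reply is that this is an omission from a condensed article whose full protocol and analysis plan are not shown, and that the analysis fits the stated aim. That aim is to validate; the primary outcomes are accuracies; the sample size is built on CI width; and no superiority hypothesis is stated. This stands as far as it goes: the plan contains no wrong comparison and rules none out. But the article does choose its comparisons and its pyuria cut-off explicitly, and it leaves out the contrast on which its own Introduction depends.

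Three stronger readings are tempting and are not supported.

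- A reader might infer that the study will be unable to say whether either approach improves on current testing. It could: one urine sample per patient is split for leucocyte count, culture and biomarkers, so both comparisons can be made from the planned data. The analysis as written simply does not make them.
- A reader might take "Categorical values will be compared using the Fisher exact test or Pearson χ2 test" as an independent-groups test misapplied to paired results. The sentence directly follows the subgroup analyses, whose groups are independent, so it is not an error.
- A reader might take Future implications as a claim that biomarkers should replace a leucocyte count. The sentence concerns the choice among biomarkers.

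It is also fair to object that the panel-versus-pyuria comparison may remain inconclusive at this sample size. That stands. It argues for estimates with CIs, not for leaving the comparison out.

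**Conclusion.** The point holds as a gap between rationale and planned analysis that should be closed before results are seen. The plan does not estimate the gain of 200 over 10/µL, or what the biomarkers add to a leucocyte count, and the 80%/80% target cannot stand in for either.

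The size differs by comparison. On the cited figures, the specificity gain of 200/µL would be well determined (50 ±7.7 points). The accompanying sensitivity loss would be only moderately determined, under an assumed value at 10/µL. The panel's 5-point specificity advantage has a half-width of 3.3 to 6.9 points and may or may not be distinguishable from zero.

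These figures assume 234 evaluable patients, 30% prevalence, every patient counted as either UTI or not, and accuracy values from older women carrying over to this cohort.

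Two features would distort a naive comparison. The reference standard includes routine urinalysis, so pyuria may be partly built into the outcome; if it applies a low leucocyte threshold (the article gives none), sensitivity at 10/µL would be high by construction. In the other direction, biomarker cut-offs are optimised in the study data while the pyuria cut-off is fixed, which favours the biomarkers.

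**What to change.** Prespecify, on data already being collected:

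1. Accuracy of pyuria at 10/µL beside 200/µL, with paired differences in sensitivity and specificity and 95% CIs (McNemar-type).
2. The AUC of the leucocyte count, and the paired AUC difference (DeLong) from it for each biomarker and for the panel. Correct the panel and the accuracy at data-derived biomarker cut-offs for optimism, for example by bootstrap.
3. Presentation of all of these as estimates with CIs, not as superiority tests.
4. A sensitivity analysis with a UTI classification that leaves out the leucocyte component. The article does not define one, so it has to be written down in advance.

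The cost is a few extra analyses, with no new samples, visits or procedures. The downside is that panel versus pyuria may prove inconclusive, and the report should say so in advance.

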### Outcome measures

The primary outcomes of this study are the diagnostic accuracy of the individual urine biomarkers (NGAL, IL-6, AZU, TIMP 2, CXCL9), a combination of biomarkers and the pyuria cut-off level of 200 leukocytes/µL. This cut-off level is based on the results of the pilot study which showed that 200 leukocytes/µL resulted in specificity of 86% while maintaining a high sensitivity of 89%.^16^ For the definition of a UTI, a recently developed international reference standard will be used, whereby patients will be categorised as having a definite UTI, probable UTI, possible UTI or no UTI.^26^ This reference standard was developed in a worldwide Delphi procedure and consists of (1) local signs/symptoms including LUTS, (2) systemic signs and symptoms, (3) routine urinalysis results and (4) culture results. In this manner, a more accurate and standardised approach is used to minimise misclassification. To investigate the relationship between biomarker levels and disease severity and recurrence, the following secondary outcomes are chosen: the duration of symptoms in days, complications including bacteremia, sepsis, septic shock defined in accordance with the quick sequential organ failure assessment score, and renal or prostatic abscess confirmed by ultrasound or CT scan, lengths of hospital stay in days and the frequency of recurrence of UTI defined by international reference standard within 2 months after inclusion.

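### With about 70 UTI cases expected and no event rate projected, Firth regression with one biomarker per model would be a cheap improvement on unqualified logistic regression for complications and recurrence

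*Protocol article*

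**What the plan says.** The Analysis of outcome measures section of the Protocol article names one method for both outcomes: for the "association between biomarker levels and complications of UTI and recurrence of UTI, logistic regression will be used". SPSS version 29 is the only software named. The sentence does not give the estimator. It does not say whether the five biomarkers enter singly or together, or whether complications are one outcome or several.

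The Outcome measures section makes both outcomes secondary. Its list of complications runs from bacteraemia through sepsis and septic shock to "renal or prostatic abscess confirmed by ultrasound or CT scan". Recurrence is counted over 2 months from inclusion. The section gives no expected frequency for any of these events.

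The Sample size section plans only for the precision of two diagnostic measures, each with a 95% confidence interval of half-width 0.10. Taking specificity as 72% and prevalence as 30%, it arrives at 110 patients. The larger requirement comes from the other measure: "using an assumption of sensitivity 76%, N would be 234". A 5% allowance for losses brings the target to 246.

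**The concern.** The information in a logistic model is governed mainly by the number of events, and here that number was never planned. Complications and recurrence of UTI can arise only among patients who have a UTI, a group of about 70 spread over hospitals, general practices and care homes. Logistic regression named without qualification is normally read as maximum likelihood. With few events, that estimator puts a true log odds ratio too far from zero on average. If the events separate perfectly on the markers, it gives no finite estimate at all.

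At stake is the stated aim of relating biomarker levels to severity and recurrence. A real association could be reported as stronger than it is, with more noise than necessary.

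**Working it through.** **1. The plan's own sample size.** Inputs from the Sample size section: z = 1.96, half-width 0.10, prevalence 0.30, sensitivity 0.76, specificity 0.72.

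- Sensitivity: 1.96² × 0.76 × 0.24 / (0.10² × 0.30) = 233.6, rounded up to 234 (stated 234).
- Specificity: 1.96² × 0.72 × 0.28 / (0.10² × 0.70) = 110.6 (stated 110).
- Drop-out: 234 × 1.05 = 245.7, rounded up to 246 (stated 246). Dividing by 0.95 would give 247; the difference does not matter here.

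**2. UTI cases.** 0.30 × 234 = 70.2 evaluable, or 0.30 × 246 = 73.8 of those enrolled. I use 70.

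**3. Events per outcome.** The rates are assumptions, because the article gives none. The last column is the exact binomial probability with n = 70.

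| Assumed rate | Expected events | P(fewer than 10 events) |
|---|---|---|
| 5% | 3.5 | 99.8% |
| 10% | 7 | 84% |
| 15% | 10.5 | 38% |
| 20% | 14 | 8% |
| 30% | 21 | 0.07% |

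**4. One marker per model, true odds ratio 2 per SD (log odds ratio 0.693).** Simulation with n = 70, a standardised normal marker and 3,000 data sets per rate. Data sets with no events or with separation are set aside and counted as not estimable. The Firth column uses the first 600 data sets.

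| Rate | Mean ML log OR | Excess | SD | Median ML OR | Firth OR (from mean log OR) | Not estimable by ML |
|---|---|---|---|---|---|---|
| 5% | 0.790 | 14% | 0.84 | 2.05 | 1.98 | 3.2% |
| 10% | 0.780 | 13% | 0.61 | 2.05 | 2.01 | 0.2% |
| 20% | 0.743 | 7% | 0.40 | 2.05 | 1.97 | 0% |
| 30% | 0.741 | 7% | 0.34 | 2.04 | 2.03 | 0% |

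The excess is (mean − 0.693)/0.693. Repeat runs that dropped data sets with fewer than 2 events gave 17–20% at a 5% rate, 8–12% at 10%, 9–11% at 15%, 6–9% at 20% and 6% at 30%. Taken together, the range is about 6–20%.

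Firth's mean log odds ratio stayed within about 3% of the truth. Its root mean squared error was lower than that of maximum likelihood: 0.62 against 0.81 at 5%, 0.47 against 0.55 at 10%, and 0.31 against 0.33 at 30%, with no loss of power.

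**5. Bias against noise.** At a 10% rate the bias is 0.780 − 0.693 = 0.087 and the SD is 0.61. The bias is then 0.087² / (0.087² + 0.61²) = 0.0076 / 0.380, or about 2% of the mean squared error. So Firth's lower error comes mostly from reduced scatter.

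**6. A marker with no association (true odds ratio 1).** The geometric mean of the estimated odds ratios was 1.00–1.01 at rates of 5–30%. Wald false-positive rates at the 5% level were 2.9%, 3.6%, 3.8%, 4.0% and 4.6% at rates of 5, 10, 15, 20 and 30%.

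**7. Where estimation fails.** With one marker at a 2% event rate, about 27% of data sets gave no estimate, mostly because there were no events. With five independent markers in one model, the failures were 56% at a 2% rate, 17% at 5% and 2% at 10%. In the five-marker model the excess in the log odds ratio at event rates of 5–20% was 19–35% with pairwise correlation 0.5, and 47% at a 5% rate with independent markers ((1.020 − 0.693)/0.693).

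**The case against.** The strongest reply is that nothing here is wrong as written. Firth regression is itself a form of logistic regression. The estimator and any rule for low event counts are details that an analysis plan commonly settles, and that plan is not shown. The outcomes are secondary, and the primary diagnostic accuracy results are untouched. With one marker per model, which the article allows, the median estimate is close to the truth, 95% intervals covered at 96–97%, and separation was rare (4 of 2,000 data sets at a 5% rate). All of that stands, and it sets the weight of the point.

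A reader might also infer more than the documents support:

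- **That few events are expected.** No rate is given. At 20–30% there would be 14–21 events. The case count is itself a planning figure and depends on which categories of the reference standard count as UTI.
- **That the odds ratios will be biased whatever the truth, or that useless markers will look prognostic.** A null marker shows no bias, and its false-positive rate is below nominal.
- **That the models may well not be estimable, or are inflated by a third or more.** Those figures need very low event rates or a joint five-marker model. The article mentions combining biomarkers only for diagnosis. For complications and recurrence it neither states nor excludes a joint model.

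What survives is narrower. The article does name a method for a stated objective. A readily available alternative had less bias and less error at the assumed rates compared, and fixing one marker per model closes off the damaging case.

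**Conclusion.** The point holds as a cheap improvement. With about 70 UTI cases and an assumed event rate of 5–20%, maximum likelihood would overstate a true log odds ratio of ln 2 per SD by about 6–20% on average, most at the lowest rate. Firth regression nearly removes this and lowers the root mean squared error by 23% at a 5% rate (1 − 0.62/0.81), 15% at 10% (1 − 0.47/0.55) and 6% at 30% (1 − 0.31/0.33). Imprecision remains the main limit under either estimator, and no estimator helps when there are no events.

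These sizes rest on assumed event rates, on the planned 30% prevalence, on analysis among UTI cases only, and on normally distributed markers. Skewed markers would change the figures.

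**What to change.** In the Analysis of outcome measures section, replace the sentence on complications and recurrence with wording such as: *Each biomarker will be related to any complication (yes/no) and to recurrence within 2 months in separate models, one biomarker per model, using Firth penalised-likelihood logistic regression with profile-likelihood 95% confidence intervals. These secondary results are exploratory.*

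The cost is one sentence and a routine for Firth models beside the standard SPSS logistic procedure. No extra patients or data are needed, and the change can be made before analysis. The downsides are that estimates are pulled slightly towards 1 compared with maximum likelihood, and that no mutually adjusted multi-marker model is reported.

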### Ethics and dissemination

This study protocol has received formal approval from the scientific committee of the LUMC in the Netherlands. The protocol was also reviewed by the local research (nWMO) committee, who declared on 15 April 2024 that the medical research involving human subject act (Dutch abbreviation: WMO) does not apply to the current study (reference number nWMODIV2_2024025). On 6 December 2024, the study received approval from the NHS Research Ethics Committee in the UK (reference number 24/LO/0649).

The dataset generated during this study will be pseudonymised and will only be available from the corresponding author on reasonable request.

We plan to publish the study findings in a peer-reviewed journal and present them at academic conferences. Additionally, the results will be disseminated to healthcare providers in both primary and secondary healthcare settings.

## Discussion

The UTI-GOLD is an observational multicentre diagnostic study with the aim to validate biomarkers for an accurate diagnosis of UTI in older people. A better diagnostic test is highly needed to improve timely and appropriate treatment of UTI in older adults and avoid the negative consequences of over- and underdiagnosis.

### Reflection on study design

One of the key strengths of this study is its performance across different real-life healthcare settings, characterised by broad inclusion criteria and recruitment from the three primary locations where UTIs are diagnosed: general practice, long-term care facilities and hospitals. This approach enhances validity and the applicability of the results to a wide population of older adults.

One of the largest challenges in all UTI studies, including the UTI-GOLD study, is the risk of misclassification due to the atypical presentation of older people and the lack of a gold standard for diagnosis. To minimise this risk, a recently developed consensus-based reference standard will be used to define UTIs. This standard was comprised by a national and international panel of UTI experts using a robust Delphi method, with a high degree of consensus. In the absence of a gold standard, this approach represents the most appropriate alternative to reduce classification bias and enhance homogeneity in UTI research.

The broadly defined inclusion criteria allow for the inclusion of patients with a wide variety of clinical presentations, comorbidities and frailty levels, representing a ‘real-world’ setting. Patients with an indwelling catheter were chosen to be excluded from the study since they are a separate patient population with a distinct pathophysiological mechanism and a different diagnostic approach. Similarly, patients with pre-existing decision-making incompetence will be excluded due to their inability to provide informed consent. Patients with delirium—a common symptom in older people with UTIs—will be eligible with a deferred informed consent procedure. This approach is essential, as patients with delirium represent the group in whom diagnostic uncertainty is greatest, and the use of a structured research reference standard enables their responsible inclusion in the study. It is important to acknowledge the unmet need for a reliable diagnostic tool to diagnose UTIs in patient populations that are excluded in the current study.

Another important consideration is the challenge of obtaining a midstream urine sample. While this is the preferred collection method to minimise contamination, it is challenging in the older population, especially in frail patients. While the study aims to collect optimal urine samples through clean-catch midstream collection, it also accepts samples that may not meet this standard. By doing so, the study avoids significant selection bias and supports the development of diagnostic tests that are not only scientifically robust but also applicable in real-world settings where ideal sample collection methods may not always be feasible.

